#### Secondary Objectives

The secondary objectives were to evaluate the effects of SDM on patients’ level of knowledge of management options with benefits and risks, anxiety, and decisional conflict compared with patients managed in centers without intervention and to evaluate the effects of SDM on the physician-patient relationship in terms of information and decision-making.

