### Design and Setting of the Study

Based on our previous work on SDM in cystic fibrosis [21] and the Consolidated Framework for Implementation Research of Damschroder et al [32], this quasi-experimental here-elsewhere study compares the populations of 3 centers receiving the intervention with those of 2 centers not receiving it (controls). The 5 centers will be studied simultaneously to reduce the risk of contamination of the control group. The evaluation will follow a mixed methods approach, combining qualitative methods (consultations observations, individual semistructured interviews with patients, and focus groups with health care professionals) with quantitative methods (self-administered questionnaires). A convergent mixed methods approach will be used, with concomitant data collection, separate analysis, and subsequent linking of results. This study conforms to the StaRi (Standards for Reporting Implementation Studies) checklist (Multimedia Appendix 1).

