### Inclusion Visit (V0)

When the patient comes to the CFRC following orally induced hyperglycemia, the physician will check the patient’s eligibility criteria. During this visit, the physician will present the study and give the patient the information note. The physician will record the patient’s nonopposition in the consultation report. The methodologist in social sciences must be informed of the patient’s inclusion by sending an email containing the patient’s first and last initials and the date of the V1 visit so that she can contact the investigating center to schedule her visit.

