### Visit V1

In the CFRCs of the control group, the physician will present the patient with information on diabetes management according to his or her usual practice. In the CFRCs in the intervention group, the physician will present the patient with information on diabetes management according to SDM (options, benefits, and risks) by using the information and decision support tool. The patient will be “activated” prior to the consultation, inviting him/her to ask questions using the “Ask 3 questions” tool. During the V1 visit for the control and intervention groups, the investigator will fill in the patient’s clinical data and SDM-Q-9 adapted to the physician immediately after the consultation. The patient fills in the questionnaires immediately after the consultation (the questionnaires are handed over by the methodologist or a member of the CFRC). The methodologist in social sciences will observe the physician-patient interaction during the consultation and complete the OPTION questionnaire; conduct an individual semistructured interview with the patient immediately after the consultation; ensure that the patient completes the SURE, CollaboRATE, SDM-Q-9, and Spielberger State-Trait Anxiety Inventory questionnaires (if the patient does not read French, the methodologist will read the questionnaires to the patient and fill them in with his/her agreement); and collect the patient’s sociodemographic characteristics.

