### Decision-Making Visit (V2)

In the CFRC control group, insulin therapy decision-making will be performed according to the physician’s usual practice. In the CFRCs of the intervention group, the decision-making visit will take place after a cooling-off period of 8 to 15 days following the V1 consultation. A discussion based on feedbacks from this period will take place between the physician and the patient, and either there is a common agreement on the decision taken (SDM) or the decision is taken by the patient or the decision is taken by the physician at the patient’s demand. During this visit, the investigator will complete the SDM-Q-9 adapted to the physician immediately after the consultation. The patient fills in the questionnaires immediately after the consultation (the questionnaires are handed over by the methodologist in social sciences or a member of CFRC). The methodologist in social sciences will observe the physician-patient interaction during the consultation and complete the OPTION questionnaire, conduct an individual semistructured interview with the patient immediately after the consultation, and ensure that the patient completes SURE, CollaboRATE, SDM-Q-9, and the Spielberger State-Trait Anxiety Inventory. If the patient does not read French, the methodologist will read the questionnaires to the patient and fill them in with his/her agreement.

In the control and intervention groups, the methodologist in social sciences will attend the face-to-face consultation (possibly by videoconference if conditions require and allow) and will conduct the individual interview with the patient immediately after the consultation. If the patient is not available, the interview can take place up to V1+48 hours. The end of the research for patients in both groups is defined by the end of the individual interview at V2 or V1 for the control group if a decision is made following the consultation.

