A Spielberger State-Trait Anxiety Inventory score will be calculated for each patient if 100% of the 20 questionnaire items have been completed. A total score between 20 and 80 (high values indicating a high level of anxiety) will then be obtained by summing the scores associated with the 20 items. For questions 3, 4, 6, 7, 9, 12, 13, 14, 17, and 18, 1 point is awarded for not at all, 2 points for somewhat, 3 points for moderately, and 4 points for very much. For questions 1, 2, 5, 8, 10, 11, 15, 16, 19, and 20, the scoring will be reversed, that is, 4 points for not at all, 3 points for a little, 2 points for moderately, and 1 point for a lot. The Spielberger State-Trait Anxiety Inventory score will be expressed as the mean and standard deviation for each group and will be compared using the Wilcoxon test.

Semistructured individual interviews designed to assess the experience of information and decision-making procedures in the control and intervention groups and the effects of SDM on patients’ and health care professionals’ experience of care in the intervention groups only will be analyzed by means of a thematic content analysis conducted using NVivo 10 (QSR International) and 2 researchers participating in the study based on the interview guide developed and previously tested with patients at the CFRC in Lyon. The focus groups conducted in the control and intervention groups designed to analyze the individual and organizational factors influencing the implementation or nonimplementation of SDM will be transcribed on the basis of notes taken during the focus groups and will be analyzed on the basis of the interview guide developed.

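### Anxiety is scored only after the consultations, so with non-randomised centres a prior difference in anxiety between the groups cannot be separated from an SDM effect

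*Protocol article*

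**What the plan says.** Under Secondary Objectives, the effects of SDM to be evaluated include "anxiety, and decisional conflict compared with patients managed in centers without intervention". Under Design and Setting of the Study, "this quasi-experimental here-elsewhere study compares the populations of 3 centers receiving the intervention with those of 2 centers not receiving it (controls"); the five centres are studied at the same time.

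The section on the inclusion visit lists an eligibility check, recording of non-opposition and notice of the V1 date to the methodologist. It also states: "During this visit, the physician will present the study and give the patient the information note". It mentions no questionnaire.

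At V1, "The patient fills in the questionnaires immediately after the consultation", and the methodologist is to "ensure that the patient completes the SURE, CollaboRATE, SDM-Q-9, and Spielberger State-Trait Anxiety Inventory questionnaires". At V2 she is again to "ensure that the patient completes SURE, CollaboRATE, SDM-Q-9, and the Spielberger State-Trait Anxiety Inventory". A control patient's participation may end at "V1 for the control group if a decision is made following the consultation".

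Under Analysis: Secondary End Points, one 20-item score from 20 to 80 is defined. The "Anxiety Inventory score will be expressed as the mean and standard deviation for each group" and compared by the Wilcoxon test. No change score or adjustment is described. The comparability check under Descriptive Analysis names age, sex, history and severity of disease for patients, but not anxiety.

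**The concern.** SDM-Q-9 and CollaboRATE rate a consultation and have no value before it. Anxiety differs: the same patient can be scored beforehand, and in this study that score is needed. By the time of the V1 form, intervention patients have had the three-question activation tool and a consultation built on the decision aid. The V1 score is therefore already an outcome and cannot serve as a baseline.

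The centre determines the group, so nothing in the design balances anxiety before V1. If patients in the three intervention centres arrive more anxious, SDM will appear to raise anxiety. If they arrive less anxious, a real rise caused by going through the risks of both options can be hidden. Once V1 has taken place the missing score cannot be recovered, and no later analysis plan can adjust for it.

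**Working it through.** **Inputs from the protocol.** 5 centres × 8 patients = 40, which reproduces the stated total; 3 × 8 = 24 intervention and 2 × 8 = 16 control. The article attaches no SD, effect size or power to anxiety, so there is no stated precision figure to reproduce.

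**Assumptions, not in the documents.** SD 11 points; correlation r between the pre-V1 and post-consultation scores 0.5 to 0.7; equal SD before and after; independent patients. Results in SD units hold for any SD.

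**Precision of the post-only comparison.**
- SE = SD × √(1/24 + 1/16) = 0.323 SD, or 11 × 0.323 = 3.55 points.
- 95% half-width = 1.96 × 3.55 = 7.0 points (0.63 SD).

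**Precision with a baseline covariate.** Residual variance is multiplied by 1 − r².
- r = 0.5: variance falls by 25%; SE = 3.55 × √0.75 = 3.07 points.
- r = 0.7: variance falls by 49%; SE = 3.55 × √0.51 = 2.54 points.

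**Bias from a starting gap, with no SDM effect.** The false difference is r × gap. A 5-point gap gives 0.5 × 5 = 2.5 to 0.7 × 5 = 3.5 points.

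**Simulation.** 24 v 16, normal scores, no SDM effect, 3,000 runs per scenario. The two ends of each range are r = 0.5 and r = 0.7.

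| Starting gap | Points at SD 11 | False difference, post-only | Wilcoxon rejects at 5% |
|---|---|---|---|
| 0 | 0 | about 0 | 4.9% to 5.5% |
| 0.25 SD | 2.75 | 0.13 to 0.17 SD | 6.3% to 7.7% |
| 0.5 SD | 5.5 | 0.25 to 0.35 SD | 11.3% to 16.6% |
| 0.8 SD | 8.8 | 0.39 to 0.58 SD | 19.5% to 38.4% |

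With the pre-V1 score as a covariate, the mean false difference stayed within 0.02 SD of zero in every scenario, and rejection lay between 4.2% and 5.6%.

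**The case against.** The strongest objection is that the control centres run concurrently under the same eligibility criteria: a diabetes-range test or a pathological glucose recording, normal fasting glucose, stable condition and both options open. Anxiety arising from the new result is expected in both groups and cancels. This stands. A reader might infer that anxiety from the diagnosis as such cannot be told apart from an SDM effect, and the documents do not support that. Only a between-group difference in prior anxiety stays confounded, and nothing in the documents shows that one exists.

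A reader might also take anxiety to be the only patient harm measured. That is not supported either: decisional conflict is measured and compared too and can worsen, and the protocol labels neither a harm.

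The visible schedule may be incomplete. Figure 1 is not shown, and the V1 and V2 lists omit the knowledge questionnaire. That is a fair caution, but no text places an anxiety form before V1. Leaving covariate adjustment to an analysis plan would be normal; leaving out the measurement cannot be repaired there.

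This is also a feasibility-sized pilot, and anxiety is secondary. At a 5-point gap the bias is no larger than the post-only standard error. That limits the importance of the point, but the article still plans a between-group test, and low precision makes a useful covariate more valuable.

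Finally, V0 is an imperfect baseline. The methodologist is only notified of the inclusion so that she can schedule her visit, and the V0-V1 interval is not stated. Both points stand, and both can be handled.

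**Conclusion.** The point holds in a limited form. As described, the anxiety contrast mixes any SDM effect with any difference in anxiety between the groups before V1, because the centres are not randomised and no earlier score is taken. Change within a patient from before SDM cannot be estimated at all.

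Under the assumed SD and correlations, a 5-point starting gap would produce a false difference of about 2.5 to 3.5 points. With no gap there is no bias and the Wilcoxon test keeps its level; the remaining loss is precision, with a standard error of about 3.6 points where 3.1 to 2.5 could be had.

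A baseline would not cure everything. Clustering within five centres and other centre differences remain. So does a difference in timing: control patients may finish at V1, while intervention patients decide at V2 after 8 to 15 days. The change is worth making before recruitment because it is cheap and cannot be made afterwards.

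**What to change.** Give the same 20-item inventory to every patient in both groups at V0, at the same point in the visit. The alternative is to give it on arrival at V1, before the patient meets the activation tool (displayed in the waiting room) and before the consultation. A centre member can hand it out when the methodologist is absent, as the V1 and V2 sections already allow for the other forms. Patients who do not read French would need the same reading help locally.

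Under Analysis: Secondary End Points, state that post-consultation anxiety will be compared between groups adjusted for this baseline score, and that change from baseline will be reported at V1 and at V2 where V2 takes place. Add the baseline score to the comparability table. Say in the report that the adjustment does not deal with centre clustering or other confounding.

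The cost is one short form for 40 patients, a small added burden, local arrangements for completing it, and short additions to the visit and analysis sections.

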### Decision-Making Visit (V2)

In the CFRC control group, insulin therapy decision-making will be performed according to the physician’s usual practice. In the CFRCs of the intervention group, the decision-making visit will take place after a cooling-off period of 8 to 15 days following the V1 consultation. A discussion based on feedbacks from this period will take place between the physician and the patient, and either there is a common agreement on the decision taken (SDM) or the decision is taken by the patient or the decision is taken by the physician at the patient’s demand. During this visit, the investigator will complete the SDM-Q-9 adapted to the physician immediately after the consultation. The patient fills in the questionnaires immediately after the consultation (the questionnaires are handed over by the methodologist in social sciences or a member of CFRC). The methodologist in social sciences will observe the physician-patient interaction during the consultation and complete the OPTION questionnaire, conduct an individual semistructured interview with the patient immediately after the consultation, and ensure that the patient completes SURE, CollaboRATE, SDM-Q-9, and the Spielberger State-Trait Anxiety Inventory. If the patient does not read French, the methodologist will read the questionnaires to the patient and fill them in with his/her agreement.

In the control and intervention groups, the methodologist in social sciences will attend the face-to-face consultation (possibly by videoconference if conditions require and allow) and will conduct the individual interview with the patient immediately after the consultation. If the patient is not available, the interview can take place up to V1+48 hours. The end of the research for patients in both groups is defined by the end of the individual interview at V2 or V1 for the control group if a decision is made following the consultation.

### Health Care Professional Focus Groups

Two focus groups will be conducted in the intervention CFRCs (one at the start of the study and one at the end) and one in each of the 2 control centers by the methodologist in social sciences on the basis of a moderation guide containing the key items on which participants will be invited to discuss (barriers, facilitators of information and decision-making, dedicated time with and without SDM, information and decision support tool, etc). The discussion group will be made up of 4-8 health care professionals (physicians, nurses, physiotherapists, dietitians, psychologists, etc) depending on the center and will be as representative as possible of the CFRC’s health care professional categories. In the intervention centers, the participating health care professionals will not necessarily have taken the e-learning training course. However, the group should be identical for both discussion groups unless a member is absent or leaves.

### Data Collection and Analysis

#### Sample Size

As this is a pilot study, 40 patients will be included and interviewed over a 12-month period. The number of patients included corresponds to the active patient file of the 5 CFRCs over the 12-month inclusion period. Five physicians (1 in each center) will be involved in this study.

#### Analysis

All patients and health care professionals included in this study are in accordance with the inclusion and noninclusion criteria. The primary end point is the adoption or nonadoption of SDM from the patient’s and health care professional’s point of view. The secondary end points are patient knowledge; patient anxiety levels; patients’ level of decisional conflict; patients’ experience of information and decision-making procedures, and more specifically of SDM implementation; effect of SDM on the physician; and individual and organizational factors influencing SDM implementation.

### Statistical Methods

#### Descriptive Analysis

A descriptive analysis of the characteristics of the patient population included (age, sex, history and severity of disease) and of the health care professionals on the CFRC teams (physicians, nurses, dietitians, psychologists, physiotherapists, etc, age, sex, profession, previous training in SDM) will be performed in the 2 study groups. Quantitative characteristics will be described by mean and standard deviation or by quartiles and minimum and maximum values depending on the shape of the distribution. Qualitative characteristics will be described by the numbers and percentages in each category. The comparability of the characteristics will be checked using the chi-square test for qualitative variables and the Wilcoxon test for quantitative variables. Data on the implementation of SDM in the intervention group will also be the subject of a descriptive analysis on the proportion of patients with at least one SDM consultation and the proportion of patients with 2 SDM consultations.

#### Analysis: Primary End Point

Adoption of SDM as perceived by the patient and measured using SDM-Q-9 will be analyzed in patients with no missing data on this criterion, although an approach to managing missing data may be considered. The frequency distribution of the 6 modalities of SDM-Q-9 will be described for each group in the patient unit. A total score will be obtained by summing the scores for each of the 9 questions. A transformation will be applied to obtain a total score between 0 and 100, with 0 indicating nonadoption of SDM as perceived by the patient and conversely 100 indicating adoption of SDM as perceived by the patient. The total score will be described in each group by mean, standard deviation, median, quartiles, and range, and will be compared between the 2 groups with a nonparametric Wilcoxon test. For patients in the intervention group, the variation in the responses to each of the SDM-Q-9 questions between the 2 consultations will be tested using the McNemar test (test adapted to paired data). Total SDM-Q-9 scores between the 2 consultations will be compared using the Wilcoxon signed-rank test. The same analysis will be performed on the health care professional unit to compare the adoption of SDM as perceived by the health care professional. Discordances between patient and health care professional responses to each of the 9 questions on SDM-Q-9 will be described and tested using the McNemar test. The total SDM-Q-9 score obtained on the patient unit and the professional unit will be compared using the Wilcoxon signed-rank test.

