#### Standard Care

Insulin therapy decisions are made according to the usual practice defined in each CFRC, with decision-making procedures specific to each center and each CFRC physician/dietitian/nutritionist/team. The decision-making process generally involves 2 consultations (Figure 1).

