## Results

Forty patients will be included (8 patients in each center), that is, 60 consultation observations (2 consultations per patient in the intervention groups given the modalities of the SDM process) will be conducted in 2025. Eight focus groups will be conducted in the 5 centers (2 groups in each intervention CFRC and 1 group in each control CFRC) in 2025. This qualitative corpus plus responses to the patient and physician questionnaires will make it possible to know whether the practice of SDM in CFRCs is increased by an implementation strategy and to analyze the experience of patients and their relatives regarding decision-making modalities. Analysis of the outcomes and experience of the implementation of SDM are of importance to identify the facilitators and barriers to SDM from patients’ and CFRCs’ point of view.

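### The intervention is assigned to 3 centres against 2, with one physician each, but the between-group tests treat the 40 patients as independent, so their p-values are too small if centres differ at all

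*Protocol article*

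**What the plan says.** Under Design and Setting of the Study, the Protocol article describes a quasi-experimental study that "compares the populations of 3 centers receiving the intervention with those of 2 centers not receiving it (controls"). Assignment is by centre and is not randomised. Training, coaching and integration into multidisciplinary meetings are all delivered to centre teams (Description of Intervention and Comparisons, components A, B and E).

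Under Results: "Forty patients will be included (8 patients in each center"). Under Sample Size: "Five physicians (1 in each center) will be involved in this study". The total of 40 comes from feasibility: "The number of patients included corresponds to the active patient file of the 5 CFRCs over the 12-month inclusion period". No significance level, power, effect size or ICC is stated.

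Under Analysis: Primary End Point, the unit is the patient: "The frequency distribution of the 6 modalities of SDM-Q-9 will be described for each group in the patient unit". The SDM-Q-9 total "will be compared between the 2 groups with a nonparametric Wilcoxon test", and it "will be analyzed in patients with no missing data on this criterion", so 40 is a maximum. The same analysis is to be repeated on the professionals' ratings. Analysis: Secondary End Points compares the OPTION, SURE, CollaboRATE and State-Trait Anxiety Inventory (STAI) scores with Wilcoxon tests, and the SURE percentage with a chi-square test. None of these tests has a centre term, and clustering is not mentioned anywhere in the article.

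**The concern.** A two-sample Wilcoxon test or a chi-square test is valid when the patients' outcomes are independent within and between groups. Here whole centres were placed in one arm or the other, so patients of one centre share a team, a physician and local habits. The article says so of usual practice, which proceeds "with decision-making procedures specific to each center and each CFRC physician/dietitian/nutritionist/team". SDM-Q-9, CollaboRATE and OPTION measure how decisions are made in the consultation, so differences between centres enter the outcome directly.

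If such differences exist, a patient-level test counts them as if they were repeated, independent evidence about the arm. The p-value is then too small. The professional-side comparison is at least as exposed, because five physicians supply the ratings.

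This matters because the primary objective is a between-group comparison, and the Results section says the qualitative material and the questionnaires together will show whether the strategy increases SDM practice.

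**Working it through.** **Inputs.** From the article: 3 intervention and 2 control centres, 8 patients per centre, one physician per centre, patient-level Wilcoxon test. Assumed, because the article gives neither: a two-sided 5% level and ICC values from 0 to 0.30.

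**The plan's own figure.** 5 × 8 = 40 patients, that is 3 × 8 = 24 against 2 × 8 = 16. This reproduces. There is no power calculation to reproduce.

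**Design effect.** With m = 8 patients per centre, DE = 1 + (m − 1) × ICC = 1 + 7 × ICC. The effective number of patients is 40/DE, and the standard error is understated by a factor √DE. An approximate true type I error is 2 × [1 − Φ(1.96/√DE)]. Example at ICC 0.10: DE = 1.70, effective number 40/1.70 = 23.5, √1.70 = 1.30, approximate error 13.3%.

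**Simulation.** Normal centre effects with variance ICC plus patient errors with variance 1 − ICC, 24 against 16 patients in five centres, no true effect, at least 20,000 replicates per ICC. The planned Wilcoxon test is set beside a t-test on the five centre means (3 df).

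| ICC | DE | Effective N | Approximate error, formula | Wilcoxon, simulated | Centre-mean t, simulated |
|---|---|---|---|---|---|
| 0 | 1.00 | 40.0 | 5.0% | 4.7–4.8% | about 5% |
| 0.01 | 1.07 | 37.4 | 5.8% | 5.6–5.7% | about 5% |
| 0.05 | 1.35 | 29.6 | 9.2% | 8–9% | about 5% |
| 0.10 | 1.70 | 23.5 | 13.3% | 13% | about 5% |
| 0.20 | 2.40 | 16.7 | 20.6% | 20% | about 5% |
| 0.30 | 3.10 | 12.9 | 26.6% | 26–27% | about 5% |

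Ranges show the spread between separate runs. At ICC 0 the Wilcoxon test holds its level, so the excess elsewhere comes from the correlation.

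**What a centre-level interval would look like.** In units of the total SD, a centre mean has variance ICC + (1 − ICC)/8. The 95% half-width for the group difference is 3.182 × √[(ICC + (1 − ICC)/8) × (1/3 + 1/2)], where 3.182 is the 97.5% point of t with 3 df.

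- ICC 0: 3.182 × √(0.125 × 0.8333) = 1.03 SD
- ICC 0.05: 3.182 × √(0.16875 × 0.8333) = 1.19 SD
- ICC 0.10: 3.182 × √(0.2125 × 0.8333) = 1.34 SD
- ICC 0.20: 3.182 × √(0.30 × 0.8333) = 1.59 SD

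Treating 40 patients as independent would give 1.96 × √(1/24 + 1/16) = 0.63 SD. The step from 0.63 to 1.03 SD at ICC 0 is purely the cost of having 3 df. Correlation adds the rest.

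**Exact tests on five centres.** There are C(5,2) = 10 ways to choose the two control centres. An exact rank-sum test therefore has a smallest two-sided p of 2/10 = 0.20. A permutation test on the absolute difference in centre means can reach 1/10 = 0.10, because the groups are unequal in size. Neither can reach 0.05.

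**The case against.** The best defence is that this is a pilot. The article calls it one, sets no significance threshold or power target, and uses a convergent mixed-methods design in which the conclusion also draws on interviews, observations and focus groups. That stands as a reason to read the p-values modestly. It does not make them right: the article names the test and the unit, so this is a stated choice and not a detail left to an analysis plan. The Results section still promises an answer on whether SDM practice is increased. The Discussion mentions the small number of centres only as a limit on generalizability.

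Several stronger readings are tempting but not supported:

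- A reader might infer that the plan's confidence intervals are too narrow. It plans no interval for the group difference, so the criticism applies to the p-values.
- A reader might infer that the study carries the information of only five observations. Five is the number of assigned units. The effective number of patients depends on the ICC and is still 37.4 at ICC 0.01.
- A reader might attribute the whole gap between 0.63 SD and 1.19 SD or more to correlation. Most of the gap at ICC 0.05 is the 3-df penalty.
- A reader might infer that no test could reach significance. A t-test on centre means can, under its normality assumption. Only the exact tests cannot.
- That each physician sees all 8 patients of the centre is a natural inference from one physician and 8 patients per centre, but the article does not say it outright. Clustering by centre does not depend on it.
- A reader might infer that a centre-level analysis would make the comparison sound. It corrects the error rate only if centre effects are exchangeable between arms, and it cannot remove differences that existed before training.

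**Conclusion.** Wrong as written. The primary patient-level comparison and the between-group secondary tests ignore assignment by centre, and their p-values are too small whenever the ICC exceeds 0. How far too small cannot be fixed from the article. The inflation is slight at ICC 0.01, but the error is about two and a half times the nominal 5% at 0.10 and about four times at 0.20. These figures rest on an assumed two-sided 5% level, the assumed ICC range, normal centre effects, complete data and equal centre sizes.

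A second limit remains whatever the test. With five non-randomised centres and one physician in each, the arm effect cannot be separated from centre and physician differences. The study can estimate a difference in SDM. It cannot confirm that the strategy caused an increase.

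**What to change.** 1. Present SDM-Q-9, OPTION, CollaboRATE, SURE and STAI results by centre, for all five centres.
2. Replace the patient-level between-group tests with an estimate of the group difference, either from centre means (t, 3 df) or from a mixed model with a random centre intercept and small-sample degrees of freedom. Report its 95% confidence interval and the ICC. Treat the professional-side comparison the same way.
3. Label any between-group p-value exploratory.
4. State in the Results and Discussion sections that arm cannot be separated from centre and physician with this design, so the study estimates and does not confirm an increase in SDM practice.

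The cost is revised wording and a modest amount of extra analysis, with no additional patients. The downside is a wide interval, with a half-width of roughly 1.0 to 1.6 SD for ICCs from 0 to 0.20, and no exact centre-level test able to reach 0.05.

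### McNemar's test is named for six-category SDM-Q-9 items without a dichotomy, and it cannot show whether patient and professional agree

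*Protocol article*

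**What the plan says.** All of this stands in one paragraph of the protocol article, Analysis: Primary End Point.

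- **Scale.** "The frequency distribution of the 6 modalities of SDM-Q-9 will be described for each group in the patient unit". The nine item scores are summed and rescaled to 0-100.
- **Change between consultations, intervention group.** "the variation in the responses to each of the SDM-Q-9 questions between the 2 consultations will be tested using the McNemar test". The only reason given for the test is that it suits paired data.
- **Professionals.** "The same analysis will be performed on the health care professional unit", so the item tests are repeated on the physician version.
- **Patient against professional.** Discordances between their "responses to each of the 9 questions on SDM-Q-9 will be described and tested using the McNemar test".
- **Totals.** "Total SDM-Q-9 scores between the 2 consultations will be compared using the Wilcoxon signed-rank test". The patient and professional totals are also compared by signed-rank test, and the two study groups by a Wilcoxon test.

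Under Analysis, "The primary end point is the adoption or nonadoption of SDM" from both viewpoints. No threshold that would make an item or the total binary appears anywhere in the article.

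**The concern.** There are two separate problems.

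**The test does not match the data.** Pairing is necessary for McNemar's test but not sufficient: it also needs two categories. Someone must therefore collapse six ordered levels into two before it can be run. The article does not say where, and the choice can be made after the data are seen. The collapse also ignores every movement that stays on one side of the cut.

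**The test does not answer the discordance question.** McNemar's test asks whether the two margins are equal, that is, whether one rater is systematically higher. It does not ask whether the two members of a pair gave the same answer. Disagreements that balance out are invisible to it.

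At stake are the item-level results on the primary instrument. They could turn on an arbitrary cut, and a non-significant discordance test could be reported as if patients and physicians saw the consultation alike.

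**Working it through.** The article gives no power, alpha or sample-size figure for these tests, so there is no figure of its own to reproduce. A two-sided 5% level is assumed below.

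**Inputs.** 40 patients, 8 per center (Results); 3 intervention and 2 control centers (Design and Setting); 5 physicians, one per center (Sample Size). This gives at most 8 × 3 = 24 pairs of consultations in the intervention group. With one complete pair per patient, it gives at most 8 × 5 = 40 patient-physician dyads. Items are scored 0-5 here for illustration.

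**Formula.** With *b* and *c* discordant pairs in the two directions, the exact two-sided McNemar p is min(1, 2 × P[X ≤ min(*b*, *c*)]), where X ~ Binomial(*b* + *c*, 0.5).

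**1. Dependence on the cut.** Suppose all 24 intervention patients move from 3 to 5 on an item.

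| Cut | b | c | Exact McNemar p |
|---|---|---|---|
| ≥1, ≥2 or ≥3 | 0 | 0 | 1.0 |
| ≥4 or ≥5 | 24 | 0 | 2 × 0.5^24 = 1.2e-7 |

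The Wilcoxon signed-rank test on the same item scores gives p = 9.6e-7 and needs no cut.

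**2. Loss of information.** Assumed scenario: 24 pairs, a latent shift of 0.6 SD, correlation 0.5, six levels. Simulated power of exact McNemar was 27% (cut ≥3), 36% (≥4) and 21% (=5), against 72-73% for the signed-rank test. Reruns under three other response distributions gave 0-34% and 66-71%. At 0.3 SD both tests are weak (about 1-9% and about 25%). At 0.9 SD McNemar reaches about 60-72% with a mid-to-upper cut. The direction is stable; the size of the gap is not.

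**3. Balanced disagreement.** Kappa = (observed − expected agreement) / (1 − expected agreement).

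| 40 dyads | b, c | Exact McNemar p | Kappa |
|---|---|---|---|
| Half disagree, evenly split | 10, 10 | 1.0 | (0.50 − 0.50)/0.50 = 0 |
| All disagree, evenly split | 20, 20 | 1.0 | (0 − 0.50)/0.50 = −1 |
| 34 agree (26 and 8), 6 disagree in one direction | 6, 0 | 2 × 0.5^6 = 0.031 | (0.85 − 0.59)/0.41 = 0.63 |

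The test is silent in the first two rows, where agreement is no better than chance or absent. It is significant in the third, where 34/40 = 85% agree. In simulation with 40 dyads and evenly split disagreement in 20% to 100% of pairs, it rejected in only 1.9% to 4.0% of samples.

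**4. The k × k extension.** Bowker's symmetry test on a 6 × 6 table has 6 × 5 / 2 = 15 degrees of freedom over 30 off-diagonal cells, with at most 24 pairs of consultations to fill them. With 12 pairs in each of two mirror-image cells its statistic is 0, so it is blind to balanced disagreement as well.

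**The case against.** The strongest defence is that these are supplementary item-level tests in a self-described pilot, and that no stated decision rests on an item-level p-value. That is right, and it limits the severity.

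A cut, or the Bowker extension, might stand in an analysis plan that is not shown, and the adoption/nonadoption wording makes a binary reading plausible. This would make the test runnable. It would not remove the dependence on the cut or, with Bowker, the sparse table, and neither route measures agreement. Where the article wants a binary score it gives the cut, as it does for SURE.

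Discordances will also be described, and a good table would show balanced disagreement. Whether professionals rate systematically higher or lower than patients is a fair question too, and a marginal test answers it. Both points stand. What remains is that the test is attached to discordance, which it does not measure. For change between consultations, net shift is the proper target, so the balanced-disagreement argument does not apply there.

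A reader might infer three stronger things that the article does not support:

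- **The total-score tests are flawed as well.** The article says only that totals will be compared, and a location test is suitable for that.
- **The item tests carry a 60% chance of a false positive** (1 − 0.95^18). That assumes a 5% level the article does not state, independence among items of one summed scale, and a count of 18 that leaves out the repeat on professionals.
- **The primary comparison fails.** It uses the total score and does not involve McNemar's test.

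**Conclusion.** The point holds and should be fixed, but it does not put the main result at risk. McNemar's test is named for items that the same paragraph treats as six-category, with no rule for making them binary. A cut can move the result from p = 1.0 to p = 1.2e-7 on the same 24 pairs. The power loss, roughly 20-36% against about 70%, is one illustration: the shift, correlation and response distribution are assumptions, not figures from the article.

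For patient-professional discordance the mismatch does not depend on coding. Neither McNemar nor Bowker detects balanced disagreement, so a non-significant result cannot be read as agreement. The between-group Wilcoxon test and the signed-rank tests on totals are unaffected.

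**What to change.** - **Change between the two consultations, patients and professionals:** replace item-level McNemar with the Wilcoxon signed-rank test on the ordinal item score.
- **Patient against professional:** report quadratic-weighted kappa or percent agreement for each item, with confidence intervals that allow for the clustering of dyads within the 5 physicians. If a paired location test is kept, describe it as a test of systematic difference only.
- **Reporting:** label item-level results as descriptive.
- **Keep** the total-score Wilcoxon and signed-rank comparisons as they are.

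Make the change before the data are analyzed, so that no cut is chosen with results in view. The cost is analysis wording and slightly more analysis work; no new data are needed. Intervals will be wide with 24 to 40 pairs and only 5 physicians, and the report should say so.
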